The Internet of things (IOT) is the name given to the network of devices and other “things” with built-in sensors, software, electronics, and network connectivity, communicating these objects over wireless networks and sending data to a cloud platform [19, 20]. The IOT medical technology would inform not only physicians but patients of real-time data to identify and early prevent issues [20–23]. Nowadays, many ventilatory devices are embedded with electronics, software, sensors, and network connectivity, which collect, provide and exchange information about compliance, ventilatory parameters, and physiological indices. With more reliable tele-monitoring and transmission technology, IOT-based management of continuous positive airway pressure (CPAP) in obstructive sleep apnea syndrome (OSA) patients, such as follow-up and tele-monitoring on adherence with the use of IOT, is emerging and yielding some positive findings [24–26]. Duiverman et al. [27] conducted the first RCT about home initiation with the help of IOT of chronic NIPPV in COPD patients recently, which demonstrated that home titration was safe and non-inferior to in-hospital titration, and reduced costs by over 50% [27].

However, clear conclusions of IOT-based home NIPPV management in COPD patients with CHRF were lacking. The primary aim of this study was to evaluate the effectiveness (in terms of Health-related Quality of Life and compliance) and safety of the IOT-based management of NIPPV for the COPD patients with CHRF. The secondary aim was to determine whether IOT-based NIPPV is more cost-effective and non-inferior to standard management of NIPPV for decreasing PaCO2, risk of mortality, and all-cause hospital readmission.

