### Sample size calculation and statistical analysis

The sample size was based on previous trials [7, 9, 10], assuming that SRI mean score was about 50 in usual NIPPV care after 1 year of treatment. We defined a non-inferiority margin of 5 for the difference in SRI mean score between the two groups, as the difference was found in previous researches about the effect of NIPPV with oxygen therapy vs oxygen therapy alone [9, 10]. On the assumption of a Standard Deviation (SD) of 20 [27] and a loss to follow-up of 25%, a sample size of 100 participants per group was needed to detect a difference of at least 5 between groups with a one-sided alpha of 0.025 and a beta of 0.1.

Continuous variables will be presented as mean and SD for normally distributed data or median and interquartile range (IQR) for nonnormally distributed data. Categorical variables will be presented as absolute numbers and percentages. Differences in continuous variables between two groups will be tested with the Student *t* tests or Mann–Whitney *U* test as appropriate.

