The categorical variables will be compared by chi-square tests or Fisher’s exact tests as appropriate. We will use a general linear repeated measures analysis of variance with a Bonferroni correction or a paired t-test to analyze assessments changes within a group over time. The primary and appropriate secondary outcome analyses, such as compliance with the ventilator, change in arterial PaCO2 and lung function, will be performed including all randomized patients according to the intention-to-treat (ITT) principle. Missing data will be handled using the “last observation carried forward” method. We will use a linear mixed model to analyze the mean difference between the groups. When the conditions for use of the linear mixed model are not appropriate, a generalized estimating equation with correction for the baseline value and minimization variables (age, body mass index, frequency of COPD readmissions over 12 months) will be used. Time from randomization to death will be performed according to the ITT principle using the Kaplan–Meier approach and the log rank test. Hazard rate will be analyzed using a Cox proportional hazards regression model adjusted for minimization covariance. When the conditions for use of are not appropriate, the time-dependent cox regression model will be used. Safety analyses will be performed on all randomized patients. Additionally, per-protocol analyses of all outcomes will be analyzed as a sensitivity analysis, including patients finishing the study according to the protocol.

Two-sided P values less than 0.05 will be considered to be statistically significant. Statistical analyses will be performed using SPSS software (version 25.0, IBM SPSS).

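### The SRI comparison is planned as non-inferiority with a 5-point margin, and non-inferiority is also an aim for PaCO2, mortality and readmission, but the only decision rule is a two-sided test of difference that never uses a margin

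*Protocol article*

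**What the plan says.** All places are in the protocol article.

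- **Background, aims.** The primary aim is broad: "The primary aim of this study was to evaluate the effectiveness (in terms of Health-related Quality of Life and compliance) and safety". It names neither superiority nor non-inferiority. The secondary aim includes showing that IOT-based care is "non-inferior to standard management of NIPPV for decreasing PaCO2, risk of mortality, and all-cause hospital readmission". No margin is given for any of these three outcomes.
- **Sample size calculation and statistical analysis, first paragraph.** "We defined a non-inferiority margin of 5 for the difference in SRI mean score between the two groups". The calculation is made "with a one-sided alpha of 0.025 and a beta of 0.1". The same sentence nevertheless describes the sample as sized to detect a 5-point difference, which is the language of a difference test.
- **Same section, analysis text.** It lists t or Mann-Whitney tests, chi-square or Fisher tests, a linear mixed model (or GEE) for the between-group mean difference, the log-rank test and Cox regression. The primary analysis is by intention to treat (ITT), and "per-protocol analyses of all outcomes will be analyzed as a sensitivity analysis". The one criterion for a conclusion is "Two-sided P values less than 0.05 will be considered to be statistically significant". The margin is not mentioned again, and no confidence bound is compared with it.
- **Abstract and Outcome and assessments.** SRI is the only primary outcome, and compliance is listed as secondary.

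**The concern.** A test of no difference and a test of non-inferiority answer different questions. A non-significant difference leaves non-inferiority open. A significant result in favour of IOT implies non-inferiority only as a by-product of superiority. As the text stands, the margin fixed at the design stage plays no part in any planned conclusion.

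Two things are at stake. First, a null result would have no stated interpretation, and a non-significant P could be taken as equivalence. Second, the sample-size paragraph speaks both of a non-inferiority margin and of detecting a difference, so it is not fixed in advance which SRI result counts as success.

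**Working it through.** **Inputs** (Sample size calculation and statistical analysis): margin 5; "On the assumption of a Standard Deviation (SD) of 20"; "a loss to follow-up of 25"%; one-sided alpha 0.025; power 0.90; 100 randomized per group. A true difference of 0 for sizing is the usual non-inferiority assumption; the article does not state one.

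**1. The plan's own figure.**
n = 2 × SD² × (1.960 + 1.282)² / 5² = 2 × 400 × 10.51 / 25 ≈ 336.2, so 337 evaluable per group. Allowing for 25% loss: 337 / 0.75 = 449.3, so 450 randomized per group. The stated 100 is not reproduced. Lower power (0.80), a one-sided 0.05 level, or an assumed true advantage of 5 points do not reach it either (336, 367 and 114 per group). This matters below only because it fixes the precision.

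**2. Is there a conflict of alpha?** No. One-sided 0.025 and two-sided 0.05 use the same critical value, 1.96. The lower bound of a two-sided 95% CI compared with -5 is exactly the one-sided 0.025 non-inferiority test. The conflict lies in the hypothesis and the decision rule.

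**3. Precision at the planned size.** Evaluable per group: 100 × 0.75 = 75.
SE = 20 × √(2/75) = 3.27. Half-width of the 95% CI = 1.96 × 3.266 = 6.40, which is wider than the margin.

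**4. What the two rules say about the same data** (difference d = IOT minus control, 75 per group):
- P > 0.05 when d lies between -6.40 and +6.40.
- Non-inferiority is shown when d - 6.40 > -5, that is, when d > +1.40.

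So every d from -6.40 to +1.40 is non-significant and fails non-inferiority, while every d from +1.40 to +6.40 is non-significant and meets it. The P value alone cannot separate them.

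**5. Error if a non-significant P were taken as non-inferiority, true difference -5.**
- 75 per group: 5 / 3.266 = 1.531. P(P > 0.05) = Φ(1.96 + 1.531) - Φ(-1.96 + 1.531) = Φ(3.491) - Φ(-0.429) = 0.9998 - 0.3340 ≈ 0.67.
- 100 per group (no loss): SE = 2.83, probability ≈ 0.58.
- Correct rule, any n: P(d - 1.96 SE > -5) = P(Z > 1.96) = 0.025.

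**6. How much of this is the rule, and how much the sample size?** At 337 evaluable per group, the size that the inputs require, power against a 5-point difference is 0.90, so the same misreading would err about 10% of the time. That is still four times 2.5%, but far below 67%. The rule is wrong at any size; the shortfall in patients makes it much worse.

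**7. PaCO2, mortality, readmission.** There is no margin, so no calculation is possible. No analysis in the article can decide these claims as written.

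**The case against.** The strongest reply is that SRI non-inferiority is nearly in place. The margin and alpha are prespecified, the mixed model estimates the mean difference, and its 95% CI bound is the required test. All that is missing is the sentence linking them, and an analysis plan not shown here may contain it. This stands in part. A reader might infer that no SRI non-inferiority claim could ever be made from this trial, but that goes too far: one added rule repairs it. What does not go away is that the article itself states a decision rule, and that rule does not match its stated margin and aims.

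Other stronger readings also lack support:

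- **That the authors will read P > 0.05 as non-inferiority.** Nothing in the article says so. It is a risk that the wording leaves open.
- **That success could be declared on compliance.** The aim wording is loose, but the Abstract and Outcome and assessments make SRI the sole primary outcome and compliance secondary.
- **That testing both non-inferiority and superiority on SRI inflates error.** It does not when both are read in that order from one 95% CI.
- **That mortality non-inferiority is unattainable.** The article gives no expected number of deaths and no margin. Assuming 30 to 60 deaths, an observed hazard ratio of 1.0 has an upper 95% limit of exp(1.96 × 2/√events), which is 2.05 down to 1.66. With 60 deaths and an observed ratio of 0.7 it is 0.7 × 1.66 ≈ 1.16. The result depends on assumptions that the article does not supply.
- **That the primary hypothesis must become superiority.** That is a debatable choice. It would discard the only stated margin and leave about 33% power for a 5-point benefit with 75 per group.

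The per-protocol analysis is planned for all outcomes. Its label as a sensitivity analysis is not itself a contradiction.

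**Conclusion.** The point holds as an internal contradiction. The article sizes SRI on a non-inferiority margin, claims non-inferiority on three further outcomes, and then gives only a two-sided difference criterion that tests none of them. For SRI this can be repaired with what is already specified. For PaCO2, mortality and readmission the claims have no margin and cannot be decided.

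The size, if a non-significant P were used in place of the margin, is a false-claim rate of about 67% (58% with no loss to follow-up) at a true 5-point deficit, against 2.5% under the correct rule. These figures rest on the article's SD of 20 and 25% loss, and on a simple two-group comparison; a baseline-adjusted model could be more precise. Most of the excess comes from the sample-size shortfall, which is a separate problem.

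**What to change.** Before any analysis by treatment group:

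1. State one primary hypothesis for the SRI score, and bring the Background aims, the sample-size paragraph and the analysis text into line with it, including the phrase about detecting a difference.
2. If the stated non-inferiority hypothesis is kept, write the rule: non-inferiority is declared only if the lower bound of the two-sided 95% CI for the mixed-model difference (IOT minus control) lies above -5. Report the per-protocol result beside the ITT result. Test superiority only afterwards, from the same CI. State that a non-significant P is not evidence of non-inferiority.
3. For PaCO2, mortality and readmission, either delete the non-inferiority wording and report estimates with 95% CIs, or give each a margin and a CI rule.
4. Reword the primary aim to match the outcome list: SRI primary, compliance secondary.

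The cost is wording in an amendment and the analysis plan. No data collection changes. The sponsor gives up secondary non-inferiority claims only where no margin can be justified. The change does not cure the sample size: with 75 evaluable per group, power to show SRI non-inferiority at a true difference of 0 stays at about 33%.

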## Discussion

The need to increase efficiency, improve the quality of life and to reduce healthcare costs has prompted the development of IOT-based home mechanical ventilation. IOT-based management of NIPPV should be available, ensuring safety, feasibility, and effectiveness to face different patients’ needs. Much more research is needed before considering IOT a real improvement.

Recently, some studies about OSA, neuromuscular or thoracic cage disease have yielded positive findings. Pinto et al. [34] showed that IOT-based tele-monitoring of compliance and ventilator parameters in amyotrophic lateral sclerosis patients offered probable favorable implications on costs, survival, and functional status, but not compliance. Furthermore, a prospective trial [25] about OSA demonstrated that tele-monitoring of CPAP uses with automated feedback messaging improved 90-day compliance in OSA patients. Pépin et al. [24] also found that a significant increase of CPAP adherence and patient-centered outcomes in favor of the multimodal tele-monitoring in OSA patients with high cardiovascular risk. Nevertheless, clear conclusions based on randomized controlled trials of IOT-based management in COPD patients with NIPPV at home are only a few. Generally, the physicians in those studies usually visit patient to solve problems as necessary [24, 26], contact through telephone or just send a message to the patient to improve use [25] in case of dissatisfactory usage or automatic alarm.

In this study, we would establish a real-time monitoring IOT cloud platform including clinical information, ventilator parameters, daily report and follow-up information. Our management teams including physicians, nurse practitioners and ventilator providers would together provide complete integrated care management based IOT cloud platform. It would be more available to face different patients’ needs and would enhance communication between patients, physicians, nurse practitioners and ventilator providers.

This study protocol has limitations which must be addressed. First, blinding of investigators was not possible due to IOT-based management of NIPPV, and it could induce bias. Nevertheless, the staff members conducting the outcome assessments would be blinded to the intervention. Moreover, all data analyses would be performed in a blinded fashion. Second, between-physicians differences in the experience of NIPPV management might affect the results of this study. IOT cloud platform would provide available information and enhance communication between patients, physicians, nurse practitioners and ventilator providers. However, the integrated care managements did not represent a criterion, but provided a personalized care. Third, appropriate adjustment of NIPPV treatment need home visit or hospitalization. Remotely adjusting of ventilator parameters was not available and needs more research. Fourth, several confounding factors associated with general therapy for stable COPD, such as pharmacologic therapy and pulmonary rehabilitation, were only suggested and not protocolized. The general therapy was to be performed in accordance with routine clinical care and pharmacologic therapy was recorded at each follow-up.

In conclusion, this study will be the first and largest randomized trial done in China to evaluate the effectiveness and safety of the IOT-based management of NIPPV for COPD patients with chronic respiratory failure. The results will improve home NIPPV treatment and management in the future.

## Trial status

Currently, participant recruitment is ongoing. Recruitment began in January 2019. The recruitment will be completed in January 2022. The results will be published as soon as possible after the analysis is completed. This protocol version number is Ver.3.

## Data Availability

During the study, the data and materials are available from the corresponding author on reasonable request. After the study, the results of this trial will be published in peer-reviewed journals and presented at national and/or international conferences.

## Abbreviations

NIPPV: Noninvasive positive pressure ventilation
COPD: Chronic obstructive pulmonary disease
IOT: Internet of things
SRI: Severe respiratory insufficiency questionnaire
CHRF: Chronic hypercapnic respiratory failure
IPAP: Inspiratory positive airway pressure
CPAP: Continuous positive airway pressure
OSA: Sleep apnea syndrome
FEV1: Forced expiratory volume in 1 s
FVC: Forced vital capacity
BiPAP: Bi-level positive airway pressure
EPAP: Expiratory positive airway pressure
4G: 4Th generation mobile communication technology
BPM: Breaths per minute
VT: Tidal volume
MRC: Medical Research Council score
CAT: COPD assessment test
cNAT: COPD nocturnal symptom assessment test
SD: Standard deviation
IQR: Interquartile range
ITT: Intention-to-treat
